## Abstract

**Background:**

Feeding practices and child undernutrition can be improved when trained health workers provide proper nutrition counseling to caregivers. However, this important management component is difficult to achieve in countries where trained health workers are limited; Tanzania is no exception. In rural and semi-urban areas, mid-level providers (MLPs) are left to manage diseases such as HIV/AIDS.

Training health workers in nutrition has been shown to be an effective intervention among HIV-negative children elsewhere, but no studies have been conducted among HIV-positive children. Furthermore, in Tanzania and other countries with MLPs, no evidence currently exists demonstrating an improvement in nutrition among children who receive health services given by MLPs. This study thus aims to examine the efficacy of nutrition training of MLPs on feeding practices and the nutrition status of HIV-positive children in Tanga, Tanzania.

**Methods/Design:**

We will conduct a cluster randomized controlled trial in care and treatment centers (CTCs) in Tanga, Tanzania. The CTCs will be the unit of randomization. We will select 16 CTCs out of 32 for this study, of which we will randomly assign 8 to the intervention arm and 8 to the control arm by coin flipping. From the selected CTCs we will attempt to recruit a total of 800 HIV-positive children aged 6 months to 14 years, half of whom will be receiving care and/or treatment in the CTCs of the intervention arm, and the other half of whom will be receiving care and/or treatment in the CTCs of the control arm (400 children in each condition).

We will provide nutrition training to MLPs of the CTCs selected for the intervention arm. In this intervention, we will use the World Health Organization guidelines on nutrition training of health workers for HIV-positive children aged 6 months to 14 years. The trained MLPs will then provide tailored nutrition counseling to caregivers of children being treated at the 8 CTCs of the intervention arm. We will measure nutrition status and child feeding practices monthly for a total of six months.

**Conclusions:**

Results of this trial will help expanding undernutrition interventions among HIV-positive children in Tanzania and other countries.

**Trial registration:**

Current Controlled Trials: ISRCTN65346364.

## Background

HIV/AIDS has exacerbated childhood undernutrition in developing countries and has led to a high mortality rate [1]; Tanzania is no exception. Among the general population of Tanzania, about 5.7% (2 million) were estimated to be living with HIV/AIDS in 2009. Meanwhile, 47.8% of children in the general population suffer from stunting or a chronic form of undernutrition [2]. Undernutrition among HIV-positive children remains a serious problem, even when antiretroviral therapy (ART) is administered [3]. In Tanzania, ART-treated, HIV-positive children were more likely to suffer from being underweight (4.6 times) and from wasting (9.6 times) compared to HIV-negative children [3].

Among HIV-positive children, undernutrition can be controlled if well-trained health workers counsel caregivers frequently [4,5]. By knowing the determinants of undernutrition in the specific population, such nutrition counseling can be carried out much more easily. The counseling may also focus on feeding behaviors and practices using locally available foods. Nutrition monitoring and early treatment of undernutrition also prevent further deterioration among children with pre-existing undernutrition. However, as the number of trained health workers in Tanzania is limited [6], such children have continued to suffer an unacceptable toll of undernutrition [3,7]. Semi-urban and rural areas bear the biggest brunt, and while mid-level providers (MLPs) are based in these areas [8], they are often not trained enough to ensure appropriate nutritional support of these children.

MLPs usually treat simple and specific diseases and perform simple surgical procedures [9]. They are health workers with 2–3 years of post-secondary school healthcare training who undertake tasks usually carried out by doctors and nurses [9]. The MLPs’ training focuses on major ailments specific to the populations they serve. In Tanzania, like in many other developing countries, such health cadres are commonly found in small cities and semi-urban and rural areas. In the 1960s, Tanzania introduced MLP cadres to solve the health workforce crisis in the country. Their training, however, lacks basic scientific components such as nutrition science as well as skills such as counseling, both of which are vital in helping people to improve their feeding practices and management of undernutrition. As a result, MLPs do not always have adequate knowledge and skills to manage child undernutrition, especially when it is complicated by HIV/AIDS.

In-service nutritional training of qualified health workers, such as medical doctors, nurses, nurse-midwives, nutritionists, and dieticians, can improve feeding practices including feeding frequency, dietary diversity, and energy intake among HIV-negative children aged 6 months to 2 years [10]. Nutrition counseling has been shown to have a positive effect on complementary feeding and nutrition status of children when it is provided by health workers who themselves received in-service nutrition training [11-13]. However, the evidence for such positive effects is only available for HIV-negative populations managed by well-trained health workers such as doctors and nurses—not MLPs. Furthermore, even in the case of well-trained health workers, the evidence base for the effectiveness of such interventions in sub-Saharan Africa is lacking. It is therefore difficult to generalize the results of the effectiveness of in-service nutrition training of qualified health workers to the HIV-positive children and health cadres below the qualified medical personnel in sub-Saharan Africa. This study’s main objectives are to examine the efficacy of nutrition training of MLPs on improving feeding practices and the nutrition status of HIV-positive children, as well as to improve the MLPs nutrition knowledge, management, and counseling skills in relation to child undernutrition, in Tanga, Tanzania.

## Methods/Design

### Study area

We will conduct this study in HIV Care and Treatment Centers (CTCs) in Tanga, in the North Eastern region of Tanzania. Tanga is a coastal region with varied climatic conditions that allow diverse food production. Even if sisal market exports are lost, Tanga remains one of the main producers of cereals and fruits, and these make up a large part of its major economic activities.

Tanga is a food secured region; however, it has an unacceptably high proportion of child undernutrition. For example, in the nationally representative survey in 2010, more than 49% of the 315 under-five children surveyed in the Tanga region were stunted [2]. Acute undernutrition among them is also rampant; about 12% of the 315 under-fives were underweight while 5.5% were suffering from wasting. The regional diversity in food production does not reflect diversity in consumption. For example, Tanga produces various cereals, fruits, vegetables, and both fresh and sea water products; however, only 59.4% of the 292 children aged 6 to 60 months sampled from the general population consumed foods rich in vitamin A [14]. The proportion of vitamin A deficiency among these children was 38.9%, iron deficiency was 36.5%, and iron deficiency anemia was 52.2% [14].

The region is also not spared by HIV/AIDS epidemic. The prevalence of HIV/AIDS in the region is estimated to be 2.4%, based on a sample of 833 adults aged 15 to 49 years old who were tested as part of a nationally representative survey [15,16]. Data of nutrition profiles of HIV-positive children in this region is not available.

CTCs are specialized clinics to care for HIV-positive people, including children. They operate under vertical HIV programs and are integrated into the existing health infrastructure [17]. In Tanga, all CTCs are located in health facilities. They provide care and treatment to HIV-positive people including voluntary counseling and HIV testing, prescribing and dispensing ART, ART adherence counseling, diagnosis and treatment of opportunistic infections, monitoring response to treatment and disease progression, behavior change promotion, and outreach services, among others [15,17]. HIV-positive people attend CTCs every month to get ART refills. In each visit, they also receive adherence counseling and monitoring, examination by clinicians, and management of opportunistic infections, if any [15,17].

Until December 2012, the Tanga region had a total of 32 CTCs. They are distributed throughout the region based on population density and the needs of specific areas. All districts have CTCs located in the district hospital and health centers. A total of 20,773 people living with HIV/AIDS were enrolled at these CTCs by the year 2009 [15]. According to regional unpublished data, about 1,800 HIV-positive children were enrolled at CTCs for care and treatment as of March 2013.

### Study design

We will conduct a cluster randomized controlled trial in Tanga, Tanzania. We will select 16 CTCs out of 32 for this study (Figure 1). The selected CTCs are located in public health facilities and have at least 20 enrolled HIV-positive children. We will use the coin-flipping method to randomly assign 8 CTCs to the intervention arm and 8 to the control arm (Figure 1). We will examine the effectiveness of nutrition training of MLPs on their nutrition knowledge, management of undernutrition, feeding practices, and the nutrition status of HIV-positive children attending CTCs. The intervention follows formative research conducted using focus group discussions and a cross-sectional study to examine factors associated with undernutrition, available foods, and local feeding practices for the children in this population. Results of the formative research are in the process of being published in another journal.

**Figure 1 F1:**
[figure not shown]
Participants selection flow chart.

#### Baseline

We will assess nutrition status and feeding practices (feeding frequency, dietary diversity, quality and quantity of food items consumed in the previous 24 hours) of the recruited children. We will investigate the burden of disease caused by opportunistic infections, diarrhea, malaria, and intestinal helminthes. We will also assess MLPs’ nutrition knowledge and skills for managing undernutrition in children living with HIV/AIDS before and after the training.

#### Intervention

We will conduct in-service nutrition training of two MLPs selected from each of the CTCs in the intervention arm, providing training on how to prevent, diagnose, and manage undernutrition based on the identified local determinants of undernutrition. The training methods will be adopted from the standard *Integrated Management of Childhood Illness*: *Counsel the Mother* handbook [18] and the *Guidelines for an Integrated Approach to the Nutritional Care of HIV*-*infected Children* (*6 months to 14 years*) [19].

At the end of the nutrition training, health workers are expected to improve in two competencies: knowledge on nutrition and feeding practices and skills on managing and providing nutrition care for HIV-positive children [19]. We will provide pre-course materials that include information on HIV/AIDS-staging, basic counseling skills, and basic information on complementary feeding of children to the MLPs.

The course structure includes 18 sessions of lectures, demonstrations, practice sessions, exercises, and role-play. According to the standard WHO training guide [19], this training will take 13 hours and 40 minutes. We will conduct this training over the course of two consecutive days. Table 1 contains the estimated duration and description of each session.

**Table 1 T1:** Nutrition training content and session duration

**Session**	**Content**	**Session duration**
Session 1	Introduction	15 minutes
Session 2	Review of pre-course materials	60 minutes
Session 3	Assess growth using growth charts	40 minutes
Session 4	Measuring growth using growth charts	30 minutes
Session 5	Listening and learning counseling skills	30 minutes
Session 6	Clinical signs of malnutrition in a child	30 minutes
Session 7	Practical session 1: Assessing and classifying a child’s weight and growth	120 minutes
Session 8	Assess child’s nutrition needs	30 minutes
Session 9	Decide on a Nutritional Care Plan	60 minutes
Session 10	What does the child eat or drink?	45 minutes
Session 11	Who feeds the child and how does the child eat?	30 minutes
Session 12	Food security	30 minutes
Session 13	Building confidence and support skills	30 minutes
Session 14	Practical session 2: Assessing and classifying a child’s nutritional status	120 minutes
Session 15	Exercise, risk factors and referral	30 minutes
Session 16	The HIV-infected child with special needs	60 minutes
Session 17	Children on antiretroviral treatment	30 minutes
Session 18	Conclusion and competencies	30 minutes

Total training duration 13 hours 40 minutes.

According to the requirements set by the training guide, we will select trainers who are experienced in teaching the IMCI guide, managing undernutrition and HIV/AIDS among children, counseling, and recommending feeding practices for children [19]. We will include one pediatrician, one nutritionist, and one psychologist in the team of trainers. They will be provided with the trainer’s guide and the participants’ guide, as well as the booklet that comes along with the other training materials [19].

The trained MLPs will provide nutrition counseling to caregivers and will separately undertake direct measures for managing undernutrition to the HIV-positive children attending the CTCs of the intervention arm on a monthly basis for six months of the follow-up period. A similar intervention will be made available for the control group after evaluating the results.

#### Follow-up

We will follow-up both intervention and control groups for 6 months. We will evaluate feeding practices, such as feeding frequency, dietary diversity, and quality and quantity of food eaten by children, as well as nutrition status, on a monthly basis for six months. For the intervention arm, we will also measure nutrition knowledge of MLPs before the training, immediately after the nutrition training, and again after the six-month observation period in order to measure the degree of knowledge decay.

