#### Midlevel providers (MLPs)

We will invite a minimum of two MLPs from each CTC of the intervention arm to take part in the nutrition training. We will also recruit a similar number of MLPs from the CTCs of the control arm. A total of 32 MLPs will participate in this study. MLPs include assistant medical officers, clinical officers, allied health workers, and nurse assistants. We will exclude all other health workers that do not fulfill the MLP criteria as per its definition. Such health workers include health promotion volunteers and non-clinician, home-based care staff.

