### Data collection

Prior to data collection, we will train research assistants on the data collection and ethical procedures. We will translate the English questionnaire into Swahili and then back-translate it to English using two independent local researchers to check that is retains its original meaning. We will use the Swahili version of the questionnaire for data collection. The trained research assistants will conduct a pre-test for the questionnaire and the interview in the Swahili language. We will collect data from August 2013 and continue to do so monthly for a period of six months. To assess changes in the MLPs knowledge, we will use the questionnaire from the training manual to collect data before and after the nutrition training.

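### Training effect on provider knowledge is to be examined, but no control-arm follow-up score is scheduled, so only an uncontrolled before-after change can be reported

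*Protocol article*

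**What the plan says.** Two places in the protocol article make MLP knowledge something the trial will evaluate. Background lists it with the main objectives: "as well as to improve the MLPs nutrition knowledge, management, and counseling skills in relation to child undernutrition". Study design, describing the randomised comparison, says: "We will examine the effectiveness of nutrition training of MLPs on their nutrition knowledge, management of undernutrition".

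MLPs are enrolled in both arms. Under Midlevel providers: "We will also recruit a similar number of MLPs from the CTCs of the control arm", and "A total of 32 MLPs will participate in this study".

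Three sections deal with when knowledge is measured.

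- **Follow-up** is the only one that names an arm: "For the intervention arm, we will also measure nutrition knowledge of MLPs before the training, immediately after the nutrition training". The same sentence adds a third test at month 6, whose stated purpose is to see how much of the knowledge has been lost.
- **Baseline** plans an assessment of MLP knowledge and management skills on either side of the training, with no arm named.
- **Data collection** names the tool, also with no arm: "we will use the questionnaire from the training manual to collect data before and after the nutrition training".

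The Intervention section offers control centres a similar programme only once the results have been evaluated. Data analysis lists two types of outcome variable, nutrition status and feeding practices. Both are measured on children.

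**The concern.** A statement about the effectiveness of training on knowledge needs a comparison with providers who were not trained. The trial has such providers, allocated at random and already enrolled, but no follow-up score is scheduled for them. A rise in the trained MLPs' scores could then be due to the training, to having met the questions before or, by month 6, to anything else that changed in the region's HIV clinics.

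Knowledge is also the first step in the trial's own logic: trained MLPs counsel caregivers, who change how they feed the children. If the child outcomes do not differ, a control-arm score would help to show whether control providers had also gained knowledge. Without one, contamination cannot be checked.

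**Working it through.** **1. Number of MLPs.** Inputs: two MLPs per care and treatment centre (CTC), from Intervention and Midlevel providers; 8 CTCs per arm, from Study design.

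2 × 8 × 2 = 32, which reproduces the stated total. Each arm has 2 × 8 = 16 MLPs. Midlevel providers gives two as a minimum per CTC, but the total of 32 fits exactly two.

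**2. Knowledge scores by arm, as written.**

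| Time | Intervention arm (16) | Control arm (16) |
|---|---|---|
| Before training | scheduled (Follow-up) | not stated; Baseline and Data collection leave it open |
| Immediately after training | scheduled (Follow-up) | none stated |
| Six months | scheduled (Follow-up) | none stated |

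The text leaves room for a control score at baseline. A baseline score alone gives no comparison after training.

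**3. What each within-arm contrast can carry.**

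- *Before to immediately after.* The training takes two consecutive days, so there is little room for secular change. Retest learning remains.
- *Before to six months.* Both retest learning and secular change remain. The tool at six months is not named. I assume it is the same questionnaire.
- *Immediately after to six months.* This is the decay question. It concerns trained MLPs only and needs no control.

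**4. What a control-arm score at month 6 would allow.** The article gives no SD and no intraclass correlation (ICC) for knowledge, so I assume an ICC of 0 to 0.5. With two MLPs per CTC and individual standard deviation σ:

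- variance of a CTC mean = σ²(1 + ICC)/2
- standard error of the difference, 8 v 8 CTCs = σ√[(2/8) × (1 + ICC)/2] = σ√[(1 + ICC)/8]

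With two-sided 5%, 80% power and 14 degrees of freedom, the noncentral t gives a detectable difference of 1.51 SD of CTC means. That is 1.51/√(2/8) ≈ 3.01 standard errors. In individual SD:

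| Assumed ICC | t, 14 df | Normal approximation |
|---|---|---|
| 0 | 1.07 | 0.99 |
| 0.1 | 1.12 | 1.04 |
| 0.3 | 1.21 | 1.13 |
| 0.5 | 1.30 | 1.21 |

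The t column is the one to use with 16 clusters. Adjustment for the baseline CTC mean could lower these values, by an amount that depends on a correlation the article does not give.

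**The case against.** The best defence is that Follow-up describes a decay series and not the whole knowledge schedule. Decay can be studied only in trained MLPs, and the sentence gives that as its purpose. Baseline and Data collection are not limited to one arm, and testing the control MLPs would be a natural reason to recruit them. A condensed article may also leave their schedule to the full protocol.

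Part of this stands. A control baseline score is not ruled out, so a reader who infers that control MLPs are never tested, or that a between-arm comparison is impossible, goes further than the text. But Follow-up does more than omit detail: it assigns all three time points to one arm. The two sections without an arm time the test by a training that controls do not receive during the trial.

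Three other strong readings also fail.

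- *Knowledge is a formal trial outcome.* Data analysis lists only child-level outcomes. Knowledge is a stated objective and effectiveness target.
- *Failed training could not be detected.* No immediate gain, or loss of the gain by six months, would show in the intervention-arm scores. Only contamination stays hidden.
- *The trial's main results are at risk.* The sample size rests on children's weight gain, and Data analysis specifies its outcomes at child level. Neither depends on the knowledge scores.

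**Conclusion.** The point holds as a mismatch between a stated aim and the measurement schedule. The article says it will examine the effect of training on MLP knowledge and enrols about 16 control MLPs, yet schedules no follow-up score for them. As written, the knowledge result is an uncontrolled before-after change in about 16 trained MLPs. It is open to retest effects throughout and to secular change at six months.

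The harm has no numerical size that the article's figures allow. The range of about 1.1 to 1.3 individual SD describes what the repaired comparison could detect. It rests on an assumed ICC of 0 to 0.5, two MLPs per CTC, complete scores and no baseline adjustment. Only a large effect would be found reliably, but the comparison needs no new recruitment. This is a cheap improvement to a provider-level objective.

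**What to change.** Amend Baseline, Follow-up and Data collection to say that the same questionnaire goes to the control-arm MLPs at baseline and month 6, and that the month-6 test in the intervention arm uses it too. Compare arms at month 6 on CTC mean scores, adjusted for the baseline CTC mean. Keep the immediate post-training score for decay within the intervention arm.

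The cost is about 16 × 2 = 32 extra questionnaires from providers already recruited, at centres where data are collected monthly. The downside is that control MLPs see the test items, which could prompt them to learn. Testing controls at month 6 only would limit this and halve the forms to 16, but would give up the baseline adjustment. In either version the intervention arm has sat the test more often by month 6 (two earlier sittings, against one or none), so retest learning is reduced but not fully balanced. The report should say so.

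If control MLPs will not be tested at follow-up, reword Study design so that the knowledge result is described as an uncontrolled before-after finding, and state what the control MLPs are recruited for.
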